### **4.2 Assessments and procedures**

#### **4.2.1 Overview**

Participants who fulfil all of the inclusion criteria and none of the exclusion criteria will be included in the study (Visit 1). As part of the registration of interest in the study, the participant must inform about their email address, mailing address and telephone number.

The participant will be contacted by the investigator by email and given a user name, which is the same as the user's e-mail address, and a password for the clinical trial web pages.

During the study the participant will be sent reminders by email for completion of the diary.

A structured sleep diary will be completed electronically every day during the whole study. At Visit 2 (Day 10) the selection criteria once more will be confirmed, and the participant's ability to complete the sleep diary will be assessed. If the participant still fulfils all selection criteria and has completed the sleep diary every day, he/she will be randomised to study treatment. Participants who at Day 14 still fulfil all selection criteria and have completed the sleep diary at least ten of the fourteen days will also be randomised to study treatment.

The study treatment will be shipped directly from a pharmacy to the participant, and the participant will start taking the treatment at Visit 3. The participant will confirm receipt of the treatment by entering the treatment number inscribed on the medicine box label into the Sleep Diary.

The treatment period will commence the first day that the participant enters the number of study medicine tablets that s/he took into the Sleep Diary and will last 14 days, at the end of which the participant will complete the Sleep Diary as usual plus three more questions. (Visit 4).

Participants will be asked to avoid using other medication for insomnia and to maintain their usual self-help strategies for their sleeping difficulties.

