#### 4.2.6 Sleep diary

Following the initial screening, potential participants will be asked to complete an electronic (web-based) sleep diary for four (two + two) weeks.

Five variables will be measured on a daily basis:

- Latency to sleep onset
- Number of night awakenings
- Total sleep time
- Quality of sleep
- Energy level the following day

These variables have been used and cited in the literature as being important measures of sleep. The response options that are used are modified from those used by Coxeter and colleagues in the following ways: We have used seven categories for all five questions for consistency and to facilitate interpretation relative to what has been found to be a clinically important mean difference on 7-point scales. We have added an additional category at the upper end of sleep latency and we have used half hour intervals for total sleep time under five hours to pick up what are likely to be meaningful differences for these two outcomes, based on clinical experience. Finally, a question on the level of perceived refreshment post-slumber is not included because feelings of grogginess are common after awakening and this question has not been found to be helpful in clinical practice.

In addition the diary will include questions about

- Adverse events
- Concomitant medication
- Number of tablets taken

An automated email message will remind participants who have not completed their sleep diary by 1 p.m. each day to do so.

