#### 4.2.7 Global assessment score

At Visit 4 each participant will be asked to indicate for each of the five listed variables and globally whether they perceived a change for the two weeks during which they took tablets compared to the two weeks before.

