### 7.2 Estimation of sample size

Self-assessed quality of sleep has been selected as the main outcome for this trial. For each participant we will calculate a mean value for the quality of sleep for the two weeks prior to being randomized and a mean value for the two weeks after the medication period has started. The proportion of participants in each group with a change in mean score of 0.5 or more will be compared under the null hypothesis claiming no difference versus the alternative hypothesis claiming a difference:

$$H_0: p_{\text{valerian}} = p_{\text{placebo}} \quad \text{versus} \quad H_1: p_{\text{valerian}} \neq p_{\text{placebo}}$$

The table below shows the number of participants needed to reject the null hypothesis, depending on which proportion that can be anticipated for the two groups. Sample size calculations are based on Pearson Chi-square 2-sided test for two proportions, with a significance level of 0.05; power set to 80% (calculations performed with SAS, PROC POWER).

| Proportion1 | Proportion2 | Actual Power | N Per Group |
|-------------|-------------|--------------|-------------|
| 0.15        | 0.25        | 0.800        | 250         |
|             | 0.26        | 0.801        | 211         |
|             | 0.27        | 0.801        | 180         |
|             | 0.30        | 0.802        | 121         |
|             | 0.35        | 0.803        | 73          |
| 0.25        | 0.35        | 0.801        | 329         |
|             | 0.40        | 0.800        | 152         |
|             | 0.50        | 0.802        | 58          |
| 0.30        | 0.40        | 0.800        | 356         |
|             | 0.50        | 0.800        | 93          |
|             | 0.55        | 0.805        | 61          |
| 0.40        | 0.50        | 0.801        | 388         |

| Proportion1 | Proportion2 | Actual Power | N Per Group |
|-------------|-------------|--------------|-------------|
|             | 0.53        | 0.800        | 230         |
|             | 0.54        | 0.801        | 199         |
|             | 0.55        | 0.800        | 173         |
|             | 0.60        | 0.800        | 97          |

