The table shows that the number to be included depends heavily on the estimates we use for the two proportions and which difference we consider important to reveal. By including about 250-275 participants in each group we would be able to reject the null hypothesis if the difference in proportions is about 10-15%.

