### 7.3 Randomisation

The randomisation scheme (in a 1:1 ratio for active:placebo) will be generated using a computerised procedure. A complete randomisation list containing details of all participant numbers and study group will be stored as essential documentation in the Trial Master File (concealed until completion of analysis).

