#### *Secondary analyses will comprise*

- Comparison of the proportion of participants reporting an improvement in mean score of 0.5 for the other four outcomes (sleep latency, number of awakenings, total sleep time, and energy level during the day) by chi-square tests
- Comparison of the proportion of participants with any improvement for each of the five outcomes by chi-square tests
- Comparison of the proportion of participants reporting improvement on the global self-assessment using two cut off points (better or much better, and any improvement) by chi-square tests
- Comparison of the mean changes in the five outcomes by two-sample t-tests.
- Comparison of the proportion of participants in each group recording one or more adverse events during the intervention compared to the run-in period by MacNamars test and a chi-square test for the between group comparison
- An explorative analysis using repeated measures analysis of variance techniques in order to reveal any difference in the profile of the five endpoints during the intervention period taking into account the baseline period. This will also comprise a possibility to evaluate a time effect, e.g. to evaluate whether the effect is different after first day of treatment compared to a later day of treatment.

In addition, we will compare the relationship between a change of 0.5, which we have defined as the minimal clinically important difference, with self-assessed improvement by testing the association of a change of  $\geq 0.5$  on each of the 5 variables in the sleep diary with self-assessed improvement for all of the participants independent of which group they were in by chi-square tests.

The P values and confidence intervals will be reported without adjustments for multiple comparisons, and will be interpreted in the light of number of comparisons that are made.

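### The pooled chi-square tests show whether a change of 0.5 is related to self-rated improvement, not whether 0.5 is a suitable minimal important change

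*Protocol*

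**What the plan says.** Protocol section 7.5, at the end of the secondary analyses, compares a diary change of 0.5, which "we have defined as the minimal clinically important difference, with self-assessed improvement by testing the association" between the two. The method is a chi-square test of association between a diary change of at least 0.5 and self-assessed improvement. It is done for each of the five diary variables, with both arms pooled. No other threshold and no measure of classification is named. The text does not say whether self-assessed improvement means the rating of the matching variable or the global rating. Nor does it say which of the two improvement cut-offs, listed earlier in the section for the between-group comparison, applies here.

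Section 4.2.6 gives the background to 0.5. Seven response categories were used for consistency and "to facilitate interpretation relative to what has been found to be a clinically important mean difference on 7-point scales", with a literature citation. The response options themselves were modified from those of an earlier trial.

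Two places describe the extra data at Visit 4. Section 4.2.1 says that "the participant will complete the Sleep Diary as usual plus three more questions". Section 4.2.7 says that each participant will "indicate for each of the five listed variables and globally whether they perceived a change".

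**The concern.** The primary endpoint and four secondary endpoints use the 0.5 cut-off, and this is the only analysis in the trial that sets 0.5 against what participants themselves call improvement. Its null hypothesis is independence. Two reports by the same person on the same two weeks of sleep can be expected to be related, so rejecting independence says little about where the threshold should lie. A reader could take a small p-value as support for 0.5 when the result is also compatible with poor classification at 0.5 and with equally good or better classification at another value.

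The Visit 4 wording matters because ratings that are not collected then cannot be recovered. If the check is meant to be variable by variable, the form must hold the variable-level ratings.

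**Working it through.** **1. The plan's own figure.** Section 7.2 uses a "Pearson Chi-square 2-sided test for two proportions, with a significance level of 0.05; power set to 80"%. For 0.15 versus 0.25, with mean proportion 0.20:

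n = [1.960·√(2·0.20·0.80) + 0.842·√(0.15·0.85 + 0.25·0.75)]² / 0.10² = (1.109 + 0.472)² / 0.01 ≈ 250 per group.

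This matches the table, as do its other 15 rows. The sample size is not at fault.

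**2. Pooled size.** Section 7.2 states: "By including about 250-275 participants in each group we would be able to reject the null hypothesis" at a difference of about 10 to 15 percentage points. Allocation is "in a 1:1 ratio for active:placebo". Pooled N is therefore 2 × 250 = 500 to 2 × 275 = 550, less any participants without a Visit 4 rating.

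**3. Power of the association test.** For a 1-df chi-square test at 0.05 the critical value is 3.841 and the non-centrality is N·phi². At N = 500:

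| phi | N·phi² | power |
|---|---|---|
| 0.10 | 5.00 | 0.61 |
| 0.15 | 11.25 | 0.92 |
| 0.20 | 20.00 | 0.994 |

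An observed phi of √(3.841/500) = 0.088 is already significant (0.084 at N = 550).

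**4. Does significance single out 0.5?** The protocol gives no correlation between diary change and self-rating, so this step rests on assumptions. Take the two as bivariate normal with correlation r, mean change 0.3, SD 0.7 and 25% rating themselves improved. Let p₁₁ be the probability of being above the cut-off and self-rated improved, and a and b the two marginal probabilities. Then phi = (p₁₁ − ab) / √[a(1−a)b(1−b)]. At N = 500, each cell gives phi and power:

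| r | cut-off 0.25 | cut-off 0.5 | cut-off 0.75 | cut-off 1.0 |
|---|---|---|---|---|
| 0.2 | 0.12; 0.74 | 0.12; 0.75 | 0.11; 0.72 | 0.10; 0.64 |
| 0.3 | 0.18; 0.97 | 0.18; 0.98 | 0.17; 0.97 | 0.16; 0.95 |
| 0.4 | 0.23; >0.99 | 0.24; >0.99 | 0.24; >0.99 | 0.22; >0.99 |

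At r = 0.4 the 0.5 cut-off has sensitivity 0.59 and specificity 0.68, although significance is almost certain. I also varied the assumptions to mean 0.5 with SD 0.8, and to 40% improved. Over all four settings and cut-offs from 0 to 1.0, power is at least 0.92 at r = 0.3, at least 0.99 at r = 0.4, and about 0.64 to 0.81 at r = 0.2. At every r, power at 0.5 is close to power at the neighbouring cut-offs.

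**5. An illustrative table of 500.** Suppose 70 participants have both a change of at least 0.5 and self-rated improvement, 105 the change only, 90 the self-rating only, and 235 neither.

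Chi-square = 500·(70·235 − 105·90)² / (175·325·160·340) = 7.92, p = 0.005.

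Sensitivity is 70/160 = 44% and specificity 235/340 = 69%. The p-value is small, yet more than half of those who call themselves improved fall below the threshold.

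**6. Visit 4 count.** Section 4.2.1 gives 3 questions; section 4.2.7 gives 5 + 1 = 6 ratings.

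**The case against.** The protocol says that 0.5 is defined and that its relationship with self-assessment will be compared. It does not claim to validate the value, so a reader who infers that it promises validation goes beyond the text. That stands. What remains is that setting a defined minimal difference against self-rating has an evident purpose, and the test serves it poorly.

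Nor is 0.5 without support: section 4.2.6 cites an external basis. The plan also limits its dependence on 0.5 through mean changes, any improvement, and the global self-assessment at two cut-offs. A randomised comparison is valid at any prespecified cut-off. All of this stands, so the stronger inference that the primary result is undermined is not supported.

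One might also say that the test would be significant at every cut-off. That depends on the assumed correlation. At r = 0.2 significance is far from certain, and failure to find an association would be informative evidence against 0.5.

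A reader might conclude that only three ratings will be collected and that the variable-level check is therefore impossible. The documents do not show this. One question can hold several items, as question 5 of the PSQI does in section 4.2.5, and the association test may need only the global rating.

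Finally, sensitivity and specificity come from the same 2×2 tables and could be added in a statistical analysis plan, which is not at hand. But the protocol itself fixes the test of association as the method, so the comment concerns what is stated and not an omission.

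**Conclusion.** The point holds as a minor, nearly free improvement. The stated tests answer whether diary change and self-rating are related, not whether 0.5 is a suitable minimal important change. The 92% power at phi 0.15 follows from the planned size of about 500. The further statement, that neighbouring cut-offs would very probably be significant too, rests on a bivariate normal model with a correlation of 0.3 or more; the protocol gives no figure for that correlation. The analysis is supplementary, and nothing here affects the primary between-group test or the sample size. The Visit 4 counts differ on their face and need reconciling, but may be no more than loose wording.

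**What to change.** In section 7.5, replace or supplement the chi-square tests with estimates pooled over arms:

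- mean diary change with 95% CI in each self-rating category;
- sensitivity and specificity of a change of at least 0.5, with 95% CIs, against both improvement cut-offs (any improvement; better or much better);
- a statement of whether the anchor is the rating of the matching variable or the global rating.

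A cut-off derived from a ROC curve is optional and should be labelled exploratory.

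Separately, align section 4.2.1 with section 4.2.7, saying how many items Visit 4 contains and, if so, that one question holds several. The form then collects the ratings that the analysis uses.

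The cost is a change of wording and slightly more analysis work on data that section 4.2.7 already plans to collect. If the form was in fact built with fewer ratings, a few extra tick-boxes are needed.

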## **7.6 Study populations**

#### *Intention-to-treat population*

Participants will be included in the primary intention-to-treat population if they have entered the randomisation code of study treatment (available to them on study treatment packs only) and have documented that they have taken the study medicine at least once with a corresponding completion of the sleep diary.

Only the intention-to-treat population will be analysed in this study.

Data for all participants will be listed, and a list of withdrawn participants, with all reasons for withdrawal, will be given. This also applies to data for those participants who - after having consented to participate - underwent screening examinations required for inclusion into the study but who - because a criterion for exclusion was met or for other reasons - were not included in the study.

## **7.7 Data collection / case report forms**

Data will be collected using an electronic, web-based sleep diary that participants will be asked to complete each day. The data entered into the diary will be automatically stored in a database. The participants email address and other identifying information will be kept in a separate database.

Participants will be asked to check that the information they enter is correct before saving it. The data will not be analysed until after the desired sample size has been reached and data has been collected for all of the included participants.

For serious adverse events, a person authorised by the investigators will enter information obtained from primary physicians into the database.

## **7.8 Data management**

Automated validation checks will be set-up, and the participants will receive automated messages when entering inconsistent data or data that need follow-up or specific action.

Two databases will be set-up; one that includes only de-identified data of the participant (the participant is registered with participant number only) and one that can identify the participant (participant identification list) but that does not include sensitive data.

# **8 REGULATORY AND ADMINISTRATIVE PROCEDURES**

## **8.1 Ethics committee**

The study will be conducted in accordance with the Edinburgh, Scotland, (2000) amendment to the Declaration of Helsinki 1964.

The Protocol and Participant Information Leaflet and Informed Consent Form will be approved by the Ethics Committee before commencement. If a protocol amendment is necessary, this will be prepared with the agreement of the investigator, signed and submitted for ethical approval. Minor amendments that do not affect the safety or conduct of the study from the participant viewpoint, and which do not significantly reduce the scientific value of the protocol, and which do not require a significant change to be made to the consent form and/or the information sheet, will not be submitted for formal ethics review. These will be sent to the Ethics committee on an 'information only' basis.

The investigator is responsible for informing the ethics committees of any serious adverse events, as described in section 6.3.2.

## **8.2 Participant Information / Informed Consent**

The investigator is responsible for giving the study participant full and adequate information about the nature, purpose, possible risk and benefit of the study. Study participants will also be notified that they are free to withdraw from the study at any time and that there is no risk associated with discontinuing to take the tablets. The participants can take as much time as they need to read and understand the information before signing (electronically).

Due to the web-based study design, only written information will be actively provided to the participant. Potential participants will be asked a series of questions to confirm that they

understand the information that is provided and will have the opportunity to contact the investigators by phone or email and ask questions before deciding whether they want to participate in the study.

The consent to study participation will be given electronically (online) at Visit 1. A second verification of interest in study participation will be obtained, as the medication will be sent as a registered letter, requiring the participant signature.

A copy of the participant information and of the Informed Consent Form in Norwegian, will be given to the participants both online and as paper-copy with the shipment of study medication, appendix 11.2.

As the study will be used for educational purposes for the TV-program audience with respect to clinical trial principles, journalists will follow some of the participants in the study. The participants will be asked upon inclusion whether they would be interested in being contacted by a journalist. It will be emphasized that this is not a prerequisite for participation and that only 4-6 participants will be contacted.

### **8.3 Participant confidentiality**

The investigators must ensure that participant's confidentiality will be maintained. CRFs or other documents to be stored in the clinical trial database will only identify participants by their study number. The investigator will keep a separate log of participant codes and names. This database will also include the electronic confirmation of the participant's consent to study participation. The sleep diary will be in a secure zone. Each participant will be able to access her or his own sleep diary and no one else's. The investigators will only have access to anonymous data in tables. When serious adverse events are registered in the sleep diary, a message will automatically be sent to the investigators, who may then obtain additional information by contacting the participant and/or the primary physician, if needed.

Any patient medical records, received from the primary physicians in relation to adverse event reporting, will be reviewed by the study monitor and possibly by other sponsor personnel or regulatory authorities, to verify adequate source documentation, accuracy and completeness of Case Report Forms. The review will be conducted with strict adherence to professional standards of confidentiality (see section 8.8).

### **8.4 Participant treatment plan**

After the individual completion of the study, the participant will be recommended to contact her primary physician for a thorough discussion about her insomnia and further treatment. Participants will be informed that, as soon as the study and analysis is completed, they will receive information by email on whether they have received placebo or valeriana.

### **8.5 GCP**

The study will be managed and conducted according to the latest international (ICH) guidelines for Good Clinical Practice. The efforts of adapting the web-based study to comply with the guidelines are discussed throughout this protocol. As the participant will not meet health care professionals face-to-face as a consequence of study participation, the procedures for adverse event reporting and obtaining of informed consent are different from other clinical trials, at the same time striving to fulfil the requirements.

